To evaluate the efficacy of Familias con Orgullo in preventing drug use and depressive symptoms, this study will use a randomized trial design with two arms (Familias con Orgullo and community practice; see study design and intervention conditions below). We hypothesize that Familias con Orgullo will be efficacious, compared to community practice, in decreasing past 90-day drug use frequency and quantity and depressive symptoms among HSMY, over 30-months and that the intervention effects on youth outcomes will be partially mediated by changes in parent support for the youth, parent acceptance, family functioning, youth stress, and sexual minority stress. In addition to our main hypothesis, this study also aims to explore whether gender and baseline levels of parent support for the youth, parent acceptance, family functioning, youth stress, and sexual minority stress moderate intervention effects on the youth outcomes. We hypothesize that gender and baseline levels of parent support for the youth, parent acceptance, family functioning, youth stress, and sexual minority stress will moderate intervention effects on youth outcomes such that youth at higher risk (e.g., families reporting higher stress, lower support, and poorer family functioning) will benefit most from Familias con Orgullo.

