#### Main effects

All analyses will be conducted in M*plus* which utilized Full Information Maximum Likelihood to handle missing data [36, 37]. To examine the efficacy of Familias con Orgullo, compared to community practice, in decreasing past 90-day drug use (frequency and quantity) and depressive symptoms among HSMY, over 30-months, we will use latent growth modeling (LGM) [38]. Growth models can be expressed in terms that are identical to multilevel models, where the first level fits each response in time to an individual-level growth model and the second level represents how the slope of outcomes (drug use and depressive symptoms) varies by condition. The second level represents the condition effect on the slope of outcomes (drug use and depressive symptoms). As recommended by Raudenbush and Bryk, we will use 2-level analysis to determine whether the mean trajectories of outcomes for Familias con Orgullo and control differ significantly over time [39]. To account for the non-independence of outcomes, we will conduct multivariate growth modeling similar to that used in evaluating a previous trial [40]. If correlations have above moderate effects (.30 < *r*) [41], we will empirically examine the distinct contributions of the intervention on each separate outcome, using false discovery rate to account for multiple comparisons. Data analysis for this hypothesis and all others will be conducted using M*plus* (v 8.8) [42].

M*plus* Monte Carlo simulation with 10000 replications [43] was used to calculate the power for the main effects outcomes using a latent growth curve model framework with one covariate (i.e., condition assignment) and missing data. With 4 time points and assuming equal sample sizes across both conditions (i.e., 153 cases in each condition) and 20% attrition rate, which is consistent with the attrition in our past studies [12], we have 80% power (assuming a Type I error = .05) to detect a regression coefficient equal to 0.12 (d = 0.36) in the regression of the slope growth factor (for both drug use and depression) on intervention condition. This is considered a small effect size [41, 43].

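### The only stated multiplicity correction for the main outcomes depends on their correlation exceeding .30; no rule is given at or below .30, and the 80% power is per outcome at an unadjusted .05

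*Protocol article*

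**What the plan says.** All of this is in the protocol article. The hypothesis in the Introduction is that the intervention is efficacious in "decreasing past 90-day drug use frequency and quantity and depressive symptoms among HSMY, over 30-months". The Main effects section repeats these outcomes and tests the effect of condition on their slopes with a latent growth model.

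That section then makes two statements about having several outcomes:

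- The default: "To account for the non-independence of outcomes, we will conduct multivariate growth modeling similar to that used in evaluating a previous trial".
- A conditional step: "If correlations have above moderate effects (.30 <" *r*), then "we will empirically examine the distinct contributions of the intervention on each separate outcome, using false discovery rate to account for multiple comparisons".

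Nothing is said about error control when the correlations are .30 or lower. The section does not say whether the correlation is between baseline scores, slopes or residuals. It also does not name the false discovery rate procedure or its level.

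The power statement in the same section reads "we have 80% power (assuming a Type I error = .05) to detect a regression coefficient equal to 0.12 (d = 0.36"). It applies this to drug use and depression alike, with 153 per arm and 20% attrition, and mentions no multiplicity adjustment.

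**The concern.** A correction for multiple tests is needed because there are several tests, each of which can support a claim. Correlation between the tests changes how much the error inflates, but it does not remove the inflation until the tests are practically the same test. The inflation is largest when the tests are independent, so a rule that brings in correction only at higher correlation has no basis in error control. Anyone following the plan with correlations of .30 or less would have two or three slope tests and no rule for what counts as evidence of efficacy.

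Two related points follow. If the correlation is computed from follow-up data, the trial's own outcomes help decide whether a correction applies, and an estimate of .29 or .31 changes the rule. And if the correction does apply, the stated power does not describe the analysis that will be done.

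**Working it through.** **Inputs (Main effects section).** d = 0.36; 153 per arm; 20% attrition, so 153 × 0.8 = 122.4 completers per arm; Type I error .05. Sidedness is not stated. The number of primary tests is two (drug use, depressive symptoms), or three if frequency and quantity are separate.

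**Assumptions made here.** A two-sample normal approximation stands in for the Mplus simulation, whose inputs are not given. The test statistics are equally correlated, at the outcome correlation r. Benjamini-Hochberg is run at .05.

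**Step 1: reproduce the plan's power.**
- Completers per arm = 2 × ((1.960 + 0.842)/0.36)² = 121.1, rounded up to 122. Then 122/0.8 = 152.5, rounded up to 153 per arm, or 306 in total, as stated.
- In the other direction, the expected z is 0.36/√(2/122.4) = 2.816, and power = Φ(2.816 − 1.960) = 80.4%.
- One-sided .05 gives 87.9% and no attrition gives 88.3%, so neither fits. The 80% therefore corresponds to an unadjusted two-sided .05 for a single outcome.

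**Step 2: family-wise error with each test at .05 and no correction.** At r = 0 it is 1 − 0.95² = 9.75% for two tests and 1 − 0.95³ = 14.3% for three. For r > 0 it is 1 minus the probability that all correlated normals lie within ±1.96.

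| r | two tests | three tests |
|---|---|---|
| 0 | 9.75% | 14.3% |
| .3 | 9.5% | 13.6% |
| .5 | 9.1% | 12.5% |
| .7 | 8.4% | 10.9% |
| .9 | 7.0% | 8.4% |

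The error falls as r rises, but slowly, and it exceeds 5% throughout. In simulation (2,000,000 draws), Benjamini-Hochberg kept the chance of any false positive, with no true effects, at about 5% or below at every r in the table.

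**Step 3: power per outcome under a correction, same N and d.**
- Strictest step (Bonferroni): two outcomes at .025, Φ(2.816 − 2.241) = 71.7%; three outcomes at .0167, Φ(2.816 − 2.394) = 66.4%.
- Benjamini-Hochberg, two outcomes, both with d = 0.36, r = 0: an outcome is rejected if both p-values are below .05, or if its own is below .025 and the other is not below .05. That gives 0.804² + 0.717 × 0.196 = 78.7%. Simulation over r from 0 to .9 gives 78.8% to 77.7%.
- Benjamini-Hochberg, two outcomes, only one responding, r = 0: 0.717 × 0.95 + 0.804 × 0.05 = 72.2%.
- Benjamini-Hochberg, three outcomes (simulation): 78.1% to 76.5% if all respond, 67.0% to 66.4% if only one does.

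**Step 4: what 80% power would require at the strictest step.** At .025, a detectable d of 0.39, or 184 randomised per arm (368 in total). At .0167, a d of 0.41, or 203 per arm (406 in total).

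**The case against.** The strongest reply is that a reader might infer that the plan withholds correction at low correlation and lets any one of three uncorrected tests carry an efficacy claim. The article does not say this. The default is a multivariate model, and false discovery rate accompanies the only separate per-outcome examination that the sentence describes. For correlations of .30 or less the text is silent. The multivariate model follows an earlier trial that is not available here, and it could carry a joint test. This stands: the defect is an unstated rule, not a stated absence of correction. It does not remove the point, because modelling outcomes jointly accounts for their correlation but does not by itself control error across slope tests. No joint test, ordering or requirement that all outcomes succeed is stated.

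Four further replies stand in part:

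- *The trigger being in the wrong direction hardly matters numerically.* Correct. For two tests the error moves only from 9.75% to 9.5% between r = 0 and r = .3. The harm lies in the level, not the gradient.
- *Three tests is the less supported count.* Correct. The article mostly speaks of drug use and depressive symptoms as two outcomes and states power for both. Frequency and quantity would probably be correlated, though the article gives no figure.
- *The data dependence is inferred.* Correct. The cut-off is fixed in advance, and the correlation could be a baseline one. The article does not say.
- *Power of 66% to 72% overstates the loss.* Correct if those figures are presented as the general result. They hold for Bonferroni or when only one outcome responds. The article plans the same effect for both outcomes. The 80% is also openly labelled as using .05, so it is not misstated.

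A condensed article may leave detail to an analysis plan. Here, however, it does state a rule, and the rule's condition is unsound.

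**Conclusion.** The point holds in this limited form. The article's one stated multiplicity correction is tied to a correlation above .30, which is not a sound basis for deciding whether to correct, and nothing is stated at or below that value. If the slopes were then each tested at .05, family-wise error would be about 9.5 to 9.75% for two outcomes, or 13.6 to 14.3% for three. The triggering correlation is undefined, so dependence on outcome data is possible but not established.

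The 80% power is per outcome and unadjusted. With Benjamini-Hochberg and an effect on all outcomes, it becomes about 78 to 79% for two or 76.5 to 78% for three. It is about 72% (two) or 66 to 67% (three) if only one responds or Bonferroni is used.

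These figures rest on the two-sample approximation, a two-sided test and equal correlation among the test statistics. Because the rule governs the main efficacy claim, it should be settled before outcome data are analysed.

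**What to change.** 1. Delete the correlation condition.
2. Name the primary slope tests, saying whether drug use frequency and quantity count as one outcome or two.
3. Apply one prespecified correction to those tests whatever their correlation, and state its level. Use Holm if family-wise control is wanted. Benjamini-Hochberg is enough if false discovery rate control is the aim, but with three outcomes it does not in general control family-wise error.
4. Keep the multivariate growth model as the joint analysis.
5. Either restate power under the chosen correction or label the 80% as per outcome and unadjusted.

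The cost is about a sentence of analysis wording and a slightly less favourable power figure. Trial conduct does not change, and the sample size need not change if the lower power, or a somewhat larger detectable effect, is accepted.

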### Familias con Orgullo

Familias con Orgullo is a multi-level, family-based intervention that targets various risk and protective factors across the different contexts that impact youth and families. For further information on the intervention development process and detail on the intervention content, please see Lozano et al. [7]. Familias con Orgullo was iteratively developed based on feedback from HSMY and their parents [7] and targets the synergistic influence of drug use and depression through improvements in family functioning, parent support for the Youth, and parent acceptance. Unlike most interventions with SMY, Familias con Orgullo places parents in the role of change agent for the family. Specifically, the parent makes changes on behalf of the family and supports changes that youth make for themselves that subsequently impacts their outcomes [7]. Further, youth learn skills to manage sexual minority stressors through emotion regulation, role plays, and development of social support networks. Familias con Orgullo consists of 14 sessions (Table 1): seven multi parent group sessions, three multi youth group sessions, and four family sessions per parent-youth dyad.

**Table 1 pone.0295683.t001:** Familias con Orgullo—Session by session overview.

Session	Description
**Family Session #1—Engagement Family Session**	Engagement of both parent and youth by applying sexual minority affirmative counseling practices, and meeting families where they are regarding acceptance of sexual minority disclosure. Problem-solve family’s perceived barriers to participation.
**Parent Group Session #1—Parental Investment in Adolescent Worlds:**	Introduction to Familias con Orgullo and review of youth sexual minority stressors in family, school, and peer worlds. Parents are made aware that disclosure and/or acceptance is a process for both parents and youth. Parents learn about drug use and depression, its contributing factors and the role of family and parenting in countering these effects (e.g., support, acceptance).
**Parent Group Session #2—Enhancing Communication and Supportive Relationships**:	Focuses on the characteristics of effective family communication and parents engage in an exercise to reinforce key communication skills. Parents discuss what it means to be supportive and accepting of sexual minority youth.

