#### Measurement modeling

A family functioning latent construct will be created consisting of two indicators (i.e., parental involvement, and communication) to create a measurement model based on a confirmatory factor analysis using SEM techniques [33, 34]. Given that only two indicators will be used to create the latent family functioning construct, we will constrain the factor loadings to be 1 for model identification [35]. In our previous studies, we have consistently found large correlations (r > .6) between these two indicators.

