To test for mediation, we will use the "product of coefficients" test described by MacKinnon, which is based on the distribution of the indirect effect of the intervention through a mediator [44]. This procedure tests whether the product of the coefficients from the intervention to the mediator (a) and from the mediator to the outcome (b) is significantly different from zero. Specifically, we will estimate paths between the intervention condition and mediators (a path), and between mediators and outcomes (b path). Because we have four time points, our first mediation analyses will fit bivariate growth curves for both mediators and outcomes and examine the role of the (latent) slope of mediators on the slope of outcomes. The product of the two pathways (path ‘a’)*(path ‘b’) is the indirect effect of Familias con Orgullo to each of the outcome trajectories through the mediators. As noted above, we will be testing whether the product (a)*(b) is statistically significantly different from zero, by comparing the observed value of (a)*(b) to the empirical distribution calculated using the bias-corrected bootstrap [45]. In addition to the mediation models, we will also test if the initial changes in mediators from baseline to the 6-month follow-up mediate the effect of intervention condition on each of the outcome trajectories.

For the mediation analysis, we used M*plus* Monte Carlo simulation with 10000 replications to calculate the power using a mediation model framework [46]. With a baseline sample size of 306 (assuming 20% attrition rate at each assessment time point), we have 80% power (assuming a Type I error = .05) to uncover a significant mediating effect when the regression coefficient of pathways ‘a’ is approximately 0.37 and ‘b’ is approximately 0.23 (i.e., R^2^ effect size were 0.27 for the relationship between intervention and mediator; i.e., path ‘a’) and mediator and outcome (i.e., path ‘b’), which is considered a small effect [41, 43].

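### Mediation is tested with bivariate growth curves and no model holds the five correlated mediators together, so an inactive construct can pass as a mediator

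*Protocol article*

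**What the plan says.** The Introduction names five constructs and expects that intervention effects "will be partially mediated by changes in parent support for the youth, parent acceptance, family functioning, youth stress, and sexual minority stress". The section on the intervention says that it works on several of them at once, "through improvements in family functioning, parent support for the Youth, and parent acceptance".

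The mediation paragraphs under Main effects set out a product-of-coefficients test, "which is based on the distribution of the indirect effect of the intervention through a mediator". On the model, "our first mediation analyses will fit bivariate growth curves for both mediators and outcomes", with the outcome slope related to the mediator slope and a*b tested by a bias-corrected bootstrap. A second analysis uses early change: "we will also test if the initial changes in mediators from baseline to the 6-month follow-up mediate the effect" on the outcome trajectories. Neither analysis mentions adjustment for the other mediators.

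The power statement has one a (about 0.37) and one b (about 0.23): "With a baseline sample size of 306 (assuming 20% attrition rate at each assessment time point), we have 80% power".

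For correlated outcomes, by contrast, the same section does plan multivariate growth modelling. It makes no such provision for the mediators.

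**The concern.** A one-mediator model does not ask whether a construct carries the effect itself. Its b path asks whether the construct's slope goes with the outcome slope, either directly or because the construct is correlated with another mediator that does the work. If the intervention also moves the construct, a*b differs from zero even when the construct does nothing. Neither correct timing nor a different bootstrap removes this.

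Correlation between these mediators is plausible. The intervention targets several together, the support and acceptance scales overlap in content, and all measures except the urine and hair samples are self-reported. The plan also expects all five to act, so fitting one of them while leaving out several active ones is the situation it anticipates.

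At stake is what may be concluded about a named family or stress process. If one construct is truly active, separate tests may declare its correlates as well, and adding the separate indirect effects would count the same pathway more than once.

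**Working it through.** **Inputs.** From the article: baseline N = 306, 20% attrition, 1:1 allocation, alpha 0.05 (taken as two-sided), a = 0.37, b = 0.23, five mediators. Assumed: a common correlation rho between mediator residuals, K omitted mediators each with b = 0.23, condition coded 0/1 and included in the outcome model, unit residual SDs, and slopes treated as error-free. The Mplus latent growth model was not rebuilt.

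**Step 1: the plan's own power.** 306 x 0.8 = 245. Take SE(a) = 2/sqrt(N) and SE(b) = 1/sqrt(N), and count mediation when both paths are significant.
- Path a: 0.37 x sqrt(245)/2 = 2.90, power 0.825.
- Path b: 0.23 x sqrt(245) = 3.60, power 0.950.
- Product: 0.825 x 0.950 = 78.4%, close to the stated 80%. A bias-corrected bootstrap simulation gave 83%.

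The stated figure is therefore consistent with a one-mediator model at N = 245.

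**Step 2: what an inactive construct borrows.** In a one-mediator model, a construct with b = 0 takes the coefficient rho x K x 0.23. The omitted mediators also add to the residual variance: s^2 = 1 + 0.23^2 x [K(1 - rho^2) + K(K - 1)(rho - rho^2)]. Its test statistic is centred on rho x K x 3.60 / s, and the declaration rate is 0.825 times the power at that value.

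| N = 245 | centre | power of b | rate |
|---|---|---|---|
| rho 0, any K | 0 | 0.05 | 4.1% |
| rho 0.1, K = 1 | 0.35 | 0.064 | 5.3% |
| rho 0.2, K = 1 | 0.70 | 0.108 | 8.9% |
| rho 0.3, K = 1 | 1.05 | 0.184 | 15.2% |
| rho 0.6, K = 1 | 2.12 | 0.565 | 46.7% |
| rho 0.3, K = 4 | 3.75 | 0.963 | 79.5% |
| rho 0.6, K = 4 | 7.61 | 1.000 | 82.5% |

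Simulation (1,500 trials per cell) agrees: 15.9% and 46.1% for K = 1 at rho 0.3 and 0.6, and 78.3% and 82.6% for K = 4. With K = 4, weak correlation is enough: 21% at rho 0.1 and 59% at rho 0.2. The ceiling is the power of path a.

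**Step 3: all five in one model.** In the same simulations at N = 245 the inactive construct was declared in about 3 to 5% of trials at every rho from 0 to 0.7.

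**Step 4: the planned bootstrap.** At N = 245 (400 trials per cell), separate models gave 8% at rho 0 with K = 1, 24% at rho 0.3 with K = 1, and 87% at rho 0.6 with K = 4. The joint model gave about 6 to 10%. The excess comes from the model and not from the bootstrap, although the planned bootstrap does not hold exactly 5% either.

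**Step 5: power cost of the joint model.** For equal correlations the variance of b is inflated by (1 + 3 rho)/[(1 - rho)(1 + 4 rho)]: 1.23, 1.67 and 2.06 at rho 0.3, 0.5 and 0.6. Dividing 3.60 by the square root of each gives centres of 3.24, 2.79 and 2.51. The power for a true mediator then falls from 78% to about 74%, 66% and 58%.

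**Step 6: overlap.** Take a chain in which condition moves support (0.5), support moves stress (0.5) and stress moves the outcome (0.5). The true mediated effect is 0.5 x 0.5 x 0.5 = 0.125. A support-only model gives 0.125 and a stress-only model gives 0.25 x 0.5 = 0.125, summing to 0.25. Simulation gave 0.247 for that sum and 0.123 for the joint total.

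**The case against.** **The one-at-a-time reading is inferred.** The article never says outright that each mediator is tested alone, and it uses the plural elsewhere. It is also a condensed account, and a joint model may stand in an analysis plan that is not shown. This stands as a caution. But the article does fix a model type, a singular mediator in the test and a single a and b in the power statement, so the point concerns what is stated.

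**The size is not in the document.** This stands. A reader might infer that the planned tests will be wrong in most trials. The article does not support that: it gives no correlation between mediators and no number of active ones. The only correlation it reports ("we have consistently found large correlations (r > .6) between these two indicators") is between the two indicators of one construct, family functioning. Rates near 90% need N = 306, which means no attrition.

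**The simplified model flatters both sides.** With mediator reliability of 0.6 (assumed), the one-at-a-time rate at rho 0.3 with one true mediator fell from 15.5% to 8.5%. A joint model of observed changes rose to 14% at rho 0.5 with four true mediators (19% at N = 306). The joint model is therefore not a guarantee of nominal error.

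**A joint model can hide a real mediator.** In the chain of Step 6 at N = 245, the upstream construct was declared in 90% of trials when tested alone and in 6% in the joint model. A reader might infer that the joint model should replace the bivariate ones. It should not, because the parent-to-youth logic of the intervention makes such chains plausible.

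**The article claims no unique effect per construct.** It hypothesises partial mediation by all five. That is correct, and it is why the remedy limits the claims and keeps the planned models.

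**Conclusion.** The concern holds in conditional form. As described, the mediation analysis cannot separate an active process from a correlated bystander, and its separate indirect effects cannot be added up. At N = 245 with the plan's a and b, the rate at which an inactive construct is declared a mediator is about 15 to 45% with one omitted true mediator and about 80% with four, if residual slope correlations are 0.3 to 0.6. It is near nominal at zero correlation, and about 5 to 9% at 0.1 to 0.2 with one true mediator. If the attrition wording means a cumulative loss (306 x 0.8^3 = 157), the same formula gives about 9 to 26% and 55 to 64%.

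These figures rest on assumed equal correlations, error-free slopes, an inactive construct that the intervention moves and that does not act through another listed mediator, and one mediator per model as the reading of the text.

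**What to change.** In the mediation paragraphs under Main effects:

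1. Keep the bivariate growth models, and describe each result as the indirect effect through that construct and its correlates.
2. For each outcome, add one joint model with condition and all five mediators, with correlated residuals. Use the slopes or, if that growth model does not converge, the changes from baseline to 6 months that are already planned.
3. Report the total and the specific indirect effects. Claim that a construct acts independently of the others only where the joint model supports it, and say that a null specific effect does not rule out a mediator that acts through another one.
4. State that the 80% mediation power applies to a one-mediator model.

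The cost is wording and one further model per outcome on data already planned. Specific effects will have wider intervals: in the simplified calculation about 3 to 5 points less power at correlation 0.3, and 10 to 20 or more at 0.5 to 0.6. They will also be sensitive to measurement error and to the causal order among the mediators.

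### The supplementary early-change mediation test names no baseline-mediator term; run as a simple change score, it loses precision on path a and can bias path b

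*Protocol article*

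**What the plan says.** The mediation text is in the Main effects section of the Protocol article, under Data analysis plan. It describes the product-of-coefficients test in general terms: "we will estimate paths between the intervention condition and mediators (a path), and between mediators and outcomes (b path").

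Two models follow. The leading one is a parallel growth model: "our first mediation analyses will fit bivariate growth curves for both mediators and outcomes and examine the role of the (latent) slope of mediators", in relation to outcome slopes. The second is given in one sentence: "we will also test if the initial changes in mediators from baseline to the 6-month follow-up mediate the effect of intervention condition on each of" (namely, each youth outcome's trajectory). That sentence does not say whether the change is a simple difference, a residualised change or a latent change, and it neither lists nor rules out covariates.

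Baseline values of the mediators exist, because families are assessed at baseline (Recruitment procedures). They appear as model terms only in the moderation paragraph of the same section. The urn randomization balances drug use and CES-D level, not any mediator (Study design).

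**The concern.** In its plain sense, a change from baseline to 6 months is a difference score, and a difference score is negatively correlated with its own baseline. Families who start with low support or acceptance tend to show more apparent improvement through regression to the mean alone. The same holds in the other direction for youth who start with high stress.

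If baseline level is also related to the outcome slope, it is a common cause of the mediator change and the slope. Randomisation protects path a from this but not path b. A distorted path b multiplied by a real path a could then be reported as mediation, or a real mediated effect could be diluted. Separately, an unadjusted change leaves avoidable variance in path a.

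**Working it through.** **Inputs from the document.** a = 0.37, b = 0.23, 306 families, 20% attrition, type I error .05 (taken as two-sided), 80% power (all Main effects); 1:1 allocation (Study design). 306 × 0.8 ≈ 245.

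**Inputs assumed.** The document does not give ρ, the baseline-to-6-month correlation of a mediator; 0.3–0.7 is used. The relation of baseline mediator to outcome slope is also not given and is varied. Mediator variances are set to 1 within arm at both visits. The slope is treated as observed without error. The full latent growth model was not rebuilt.

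**1. The plan's own power figure.** Joint significance of the two paths with residual SDs of 1:
- SE(a) = √(4/245) = 0.128, so Φ(0.37/0.128 − 1.96) = 0.825.
- SE(b) = 1/√245 = 0.064, so Φ(0.23/0.064 − 1.96) = 0.950.
- The product is 0.784. With total variances of 1 it is 0.799.

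The stated 80% therefore reproduces. That calculation contains neither a change score nor a baseline term, so it does not show how the early-change model will be specified.

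**2. Path a.** The error variance of the arm contrast is 2(1−ρ)·4/N for the raw change and (1−ρ²)·4/N with baseline adjustment. The ratio of adjusted to raw is (1+ρ)/2. Power at N = 245:

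| ρ | Raw change, a = 0.37 mediator SD | Adjusted | Raw change, a = 0.37 change-score SD | Adjusted |
|---|---|---|---|---|
| 0.3 | 68.7% | 85.9% | 82.5% | 94.9% |
| 0.5 | 82.5% | 91.7% | 82.5% | 91.7% |
| 0.7 | 96.2% | 98.2% | 82.5% | 88.1% |

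Both estimators of path a are unbiased because condition is randomised. In mediator-SD units the gain is 17 points at ρ = 0.3 but only 2 at ρ = 0.7.

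**3. Path b.** Let the slope be S = b·M6 + g·M0 + e, with D = M6 − M0. Within arm, cov(M6, D) = 1−ρ, cov(M0, D) = −(1−ρ) and var(D) = 2(1−ρ). Regressing S on condition and D without M0 gives (b − g)/2, so the bias is −(b + g)/2. The correlation of D with M0 is −√((1−ρ)/2): −0.59, −0.50 and −0.39 at ρ = 0.3, 0.5 and 0.7.
- True b = 0.23, g = 0: unadjusted 0.115.
- True b = 0.23, g = +0.10: 0.065; g = −0.10: 0.165.
- True b = 0, g = ±0.23: ∓0.115.
- g = −b (the slope depends only on the change itself): no bias.

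With M0 in the model, the true b is recovered in every case.

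**4. False mediation (true b = 0), joint significance by simulation, N = 245, ρ 0.3–0.7.** For a baseline–slope correlation of 0.1, about 7–12% unadjusted. For 0.2, about 19–35% (another run gave 38% at ρ = 0.3). With adjustment the rate is about 4–6% throughout.

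**5. Joint power with a = 0.37 and b = 0.23, unadjusted → adjusted.**

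| Assumed data model | ρ = 0.3 | ρ = 0.5 | ρ = 0.7 |
|---|---|---|---|
| Slope depends on the 6-month residual given baseline; a in change-score SDs, b per residual SD | 69% → 90% | 73% → 87% | 75% → 83% |
| Slope depends on the change itself; effects in change-score SDs | 79% → 79% | 79% → 81% | 78% → 81% |
| Slope depends on the 6-month value (g = 0); effects in mediator SDs | 38% → 79% | 35% → 80% | 27% → 71% |
| Slope depends on the change itself (g = −b); effects in mediator SDs | 67% → 78% | 78% → 80% | 75% → 70% |

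The gain depends strongly on the data model. In the last row at ρ = 0.7 adjustment costs about 5 points: path a is already near full power there, and the added covariate widens the standard error of path b.

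**The case against.** The strongest reply is that the article never says the change is raw or unadjusted. Its one sentence also fits a residualised or latent change model that conditions on baseline. The two-path description is a generic account of the method placed before both models, not a covariate list. A condensed article may leave that detail to the full protocol or analysis plan. This stands: a reader might infer that the trial will use an unadjusted difference score, but the document does not establish it. What remains is that the mediator is defined as a change and no baseline term is named for it, while baseline terms are spelled out for moderation.

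A reader might also infer that the trial itself predicts the confounding, since the Introduction expects that "youth at higher risk (e.g., families reporting higher stress, lower support, and poorer family functioning) will benefit most from Familias con Orgullo". That is a condition-by-baseline interaction. It does not say that baseline level predicts the slope in both arms, which is what the false-mediation figures assume, and an additive baseline covariate would not model the interaction.

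Third, the sizes rest on assumed correlations and an error-free slope. An imperfectly measured slope would shrink the false-mediation rates without removing the bias. If the slope truly depends on the change itself, path b needs no adjustment and the power gain nearly vanishes or, in one configuration, reverses slightly. This also stands, so no single figure should be quoted as the effect.

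Finally, partial mediation is part of the main hypothesis, and a reader might conclude that the hypothesis depends on this test. It does not: the parallel growth-curve model comes first and this test is additional.

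**Conclusion.** The point holds in conditional form. If the early-change test is run as a simple change score, path a is unbiased but less precise for any ρ below 1, and the loss is small when ρ is high. Path b is biased by −(b + g)/2 unless the slope depends only on the change.

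Under assumed baseline–slope correlations of 0.1–0.2 and ρ of 0.3–0.7, false mediation is roughly 7–35% against about 5% with adjustment. With effects scaled to the change score, joint power rises by about 0–22 points. With effects in mediator SDs the difference ranges from a loss of about 5 points to a gain of about 45. The case for adjusting therefore rests mainly on protecting path b, with power as a likely but not guaranteed benefit.

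This is a low-cost improvement to a supplementary analysis. It does not touch the main efficacy analysis or the stated 80% mediation power, which reproduces.

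**What to change.** State that the early-change model includes the baseline mediator as a covariate in both equations:
- Path a: 6-month mediator (or its change) on condition and baseline mediator.
- Path b: outcome trajectory on condition, 6-month mediator (or its change) and baseline mediator.

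Report the indirect effect from that model. Using the 6-month value or the change gives the same a and b once baseline is included, because the two differ only by the baseline term.

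The cost is one sentence in the plan and one observed covariate per mediator model. The data are already collected and the sample size does not change. If the full analysis plan already conditions on baseline, a sentence confirming this closes the point.
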